## Abstract

**Background:**

Chronic mesenteric ischemia (CMI) is the result of insufficient blood supply to the gastrointestinal tract and is caused by atherosclerotic stenosis of one or more mesenteric arteries in > 90% of cases. Revascularization therapy is indicated in patients with a diagnosis of atherosclerotic CMI to relieve symptoms and to prevent acute-on-chronic mesenteric ischemia, which is associated with high morbidity and mortality. Endovascular therapy has rapidly evolved and has replaced surgery as the first choice of treatment in CMI. Bare-metal stents (BMS) are standard care currently, although retrospective studies suggested significantly higher patency rates for covered stents (CS). The Covered stents versus Bare-metal stents in chronic atherosclerotic Gastrointestinal Ischemia (CoBaGI) trial is designed to prospectively assess the patency of CS versus BMS in patients with atherosclerotic CMI.

**Methods/design:**

The CoBaGI trial is a randomized controlled, parallel-group, patient- and investigator-blinded, superiority, multicenter trial conducted in six centers of the Dutch Mesenteric Ischemia Study group (DMIS). Eighty-four patients with a consensus diagnosis of atherosclerotic CMI are 1:1 randomized to either a balloon-expandable BMS (Palmaz Blue with rapid-exchange delivery system, Cordis Corporation, Bridgewater, NJ, USA) or a balloon-expandable CS (Advanta V12 over-the-wire, Atrium Maquet Getinge Group, Hudson, NH, USA). The primary endpoint is the primary stent-patency rate at 24 months assessed with CT angiography. Secondary endpoints are primary stent patency at 6 and 12 months and secondary patency rates, freedom from restenosis, freedom from symptom recurrence, freedom from re-intervention, quality of life according the EQ-5D-5 L and SF-36 and cost-effectiveness at 6, 12 and 24 months.

**Discussion:**

The CoBaGI trial is designed to assess the patency rates of CS versus BMS in patients treated for CMI caused by atherosclerotic mesenteric stenosis. Furthermore, the CoBaGI trial should provide insights in the quality of life of these patients before and after stenting and its cost-effectiveness. The CoBaGI trial is the first randomized controlled trial performed in CMI caused by atherosclerotic mesenteric artery stenosis.

**Trial registration:**

ClinicalTrials.gov, ID: NCT02428582. Registered on 29 April 2015.

**Electronic supplementary material:**

The online version of this article (10.1186/s13063-019-3609-8) contains supplementary material, which is available to authorized users.

## Background

Chronic mesenteric ischemia (CMI) is the result of insufficient blood supply to the gastrointestinal (GI) tract and is caused by atherosclerotic stenosis of one or more mesenteric arteries in > 90% of cases [1, 2]. The mesenteric arteries are the celiac artery (CA), superior mesenteric artery (SMA) and inferior mesenteric artery (IMA). Classic symptoms of CMI are postprandial abdominal pain and weight loss due to fear of eating. However, CMI may present atypically with constant abdominal discomfort, nausea, vomiting, diarrhea or even constipation [1]. The “classic triad” of CMI consisting of postprandial abdominal pain, weight loss and abdominal bruit is present in only 16–22% of patients [3, 4].

The diagnosis of CMI is established by consensus in a multidisciplinary meeting joined by vascular surgeons, gastroenterologists and interventional radiologists [1]. Consensus is an accepted method of diagnosing if a gold standard test is absent [5]. Symptoms alone do not predict the diagnosis of CMI accurately [4, 6, 7]. Therefore, consensus diagnosis is based on the combination of clinical symptoms, radiological evaluation of the mesenteric vasculature and, if available, assessment of mucosal ischemia with a functional test such as gastric-jejunal tonometry [3, 8, 9] or visible light spectroscopy (VLS) [10, 11]. A definitive diagnosis of CMI is established if successful therapy of patients with CMI consensus diagnosis results in a durable relief of presenting symptoms.

Revascularization therapy is indicated in patients with a diagnosis of atherosclerotic CMI to relieve symptoms and to prevent acute-on-chronic mesenteric ischemia, which is associated with high morbidity and mortality. Endovascular revascularization has largely replaced open surgical revascularization [1, 12, 13]. Endovascular revascularization of the mesenteric arteries is achieved by means of stent placement. The SMA and CA are target vessels for therapy because of their larger diameter compared to the IMA. Furthermore, a protective collateral network ensures blood supply when the IMA is occluded as shown in patients with an aortic stent occluding the IMA. Literature on revascularization of the IMA is scarce. A study reported successful stenting of the IMA in four patients who were not candidates for CA or SMA revascularization [14]. The classic percutaneous approach for mesenteric endovascular procedure is trans-brachial and trans-femoral, but a trans-radial approach is currently gaining popularity [15].

Endovascular revascularization is associated with a significant decreased risk of in-hospital complications compared to open mesenteric surgical revascularization [16]. Despite the advantages of endovascular revascularization short term, restenosis is a common event occurring in 28–55% of patients within 2 years after endovascular mesenteric stenting [13, 17] whereas 0–25% of surgically treated patients develop restenosis [2, 18]. The primary patency rate of open surgical revascularization is significantly higher than that of endovascular revascularization (cumulative odds ratio (OR) 3.57, 95% confidence interval (CI) 1.82–6.87, *p* = 0.0002, [19].

Currently, balloon-expendable bare-metal stents (BMS) are standard care for mesenteric endovascular revascularization [1, 20]. Retrospective data, however, showed significantly higher primary patency rates of balloon-expendable covered stents (CS) at 3 years for mesenteric artery stenosis [21]. Furthermore, patients treated with CS had less restenosis, symptom recurrence and re-intervention than patients treated with BMS [21]. The Covered versus Balloon Expandable Stent Trial (COBEST) showed significantly higher patency rates of CS than BMS for aortoiliac arterial disease 18, 24, 48 and 60 months after stent placement [22, 23]. Possibly, the membrane that covers the vascular atherosclerotic lesion functions as a physical barrier for intimal hyperplasia and is, therefore, associated with less restenosis in contrast with BMS. The performance of CS for mesenteric artery stenosis is promising, but prospective confirmation is lacking. The CoBaGI trial is a multicenter, randomized controlled, patient- and investigator-blinded clinical trial designed to compare patency rates of the CS versus standard care therapy with BMS in patients with CMI based on atherosclerosis.

### Study hypothesis

CS have a significantly higher patency rate than BMS in patients with CMI due to stenosis of the CA and/or SMA of atherosclerotic origin.

## Methods/design

This study protocol is written according to the Standard Protocol Items: Recommendations for Interventional Trials (SPIRIT) 2013 Statement for study protocols of clinical trials [24]. The SPIRIT Diagram is shown as Table 1 and the SPIRIT Checklist is added in Additional file 1.

**Table 1 Tab1:** Schedule of enrollment, interventions and assessments for the CoBaGI trial according to Standard Protocol Items: Recommendations for Interventional Trials (SPIRIT) [24]

	Study period						
	Enrollment	Allocation	Post allocation				Close-out
Time point	−t_1_	0	t_1_	t_2_	t_3_	t_4_	t_x_
Enrollment:							
Eligibility screen	X						
Informed consent	X						
Allocation		X					
Interventions:							
Intervention CS			X				
Intervention BMS			X				
Assessments:							
CTA	X			X	X	X	
EQ-5D-5 L	X			X	X	X	
SF-36	X			X	X	X	
Cost-effectiveness	X			X	X	X	
SAE				X	X	X	X
Mortality				X	X	X	X

−t_1_ = screening and enrollment, t_1 =_ endovascular-stent placement, t_2_ = 6 months, t_3_ = 12 months, t_4_ = 24 months after intervention, t_x_ = end of follow-up at 24 months

*BMS* bare-metal stent, *CS* covered stent, *CTA* computed tomography angiography, *SAE* serious adverse event, *SF-36* 36-item Short Form Health Survey

### Study design

The CoBaGI trial is a randomized controlled, parallel-group, patient- and investigator-blinded, superiority, multicenter trial conducted in six centers of the Dutch Mesenteric Ischemia Study group (DMIS). Patients with atherosclerotic CMI will be randomly allocated to standard care therapy using a BMS (Palmaz Blue with rapid-exchange delivery system, Cordis Corporation, Bridgewater, NJ, USA) or a CS (Advanta V12 over-the-wire, Atrium Maquet Getinge Group, Hudson, NH, USA).

### Study setting

The CoBaGI trial is conducted within the framework of the DMIS. Six Dutch centers participate in the CoBaGI trial. The initiating center is Erasmus MC University Medical Center, an academic hospital in Rotterdam together with Medisch Spectrum Twente in Enschede which serves as a CMI-specialized referral center. Furthermore, four other Dutch tertiary referral centers participate in the study: Maasstad Hospital in Rotterdam; St. Antonius Hospital in Nieuwegein; Bernhoven Hospital in Uden, and Jeroen Bosch Hospital in ‘s-Hertogenbosch.

### Eligibility criteria

Patients with a consensus diagnosis of atherosclerotic CMI eligible for endovascular-stent placement will be included in this trial.

Inclusion criteria are:
A consensus diagnosis of CMI based on atherosclerotic mesenteric artery stenosis at the origin of the CA and/or SMA, established in a multidisciplinary meeting attended by a gastroenterologist, interventional radiologist and vascular surgeon. This consensus diagnosis is based on:
Typical symptoms (presence of postprandial pain, unexplained weight loss)Significant stenosis of > 50% of at least one of the mesenteric arteries on previous computed tomography angiography (CTA)*Functional assessment of mucosal ischemia with VLS or tonometryAged ≥18 years oldSigned informed consentTotal length of mesenteric stenosis < 25 mm

*Requirements for CTA are: CTA performed within the year before consensus diagnosis  maximum slice thickness 1 mm, enhancement in aorta 300HU.

Exclusion criteria are:
Absence of informed consentAged < 18 years oldNo stenosis detected during angiographyRenal insufficiency (glomerular filtration rate (GFR) below 30 ml/min or GFR below 60 ml/min in the presence of comorbidities relevant to renal function)Previous stent placement in the target vesselPregnancyStenosis based on median arcuate ligament syndrome (MALS)Stenosis based on vasculitisOther criteria which the physician considers incompatible with inclusion in this trial

### Recruitment and consent

Patients with CMI based on atherosclerotic mesenteric artery stenosis are eligible for the CoBaGI trial. A gastroenterologist, surgeon or research physician will screen the patient according to the inclusion and exclusion criteria. When the patient is eligible for study inclusion, the treating physician will inform the patient about the possibility of participating in the CoBaGI trial and will hand out the patient information form (Additional file 2). Furthermore, the treating physician will inform the patient that study participation is voluntary and that participation may be withdrawn at any time without the need of having to provide a reason. At the return visit, the patient is given the opportunity to ask questions. If the patient consents to participate in the CoBaGI trial, written informed consent is obtained.

### Randomization

Patients are 1:1 randomized for a BMS or CS with a web-based randomization module (9 Knots Business Solutions Ltd., Mansfield, UK) in random blocks of four or six stratified by center.

### Interventions

At the start of the endovascular procedure patients are randomized for either a BMS or CS. The approach of the intervention is at the discretion of the attending interventionalist (femoral, brachial, radial or retrograde). During the angiography the stenoses are assessed and if a suspected stenosis is not significant, this vessel will not be treated. If the stenosis is detected to be significant during angiography and the stenosis length is < 25 mm the stenosis will be treated with the allocated stent. In case multiple stenosis are present and eligible for inclusion (i.e., CA and SMA), the same allocated stent type is used. After completion of the intervention various procedural details, such as duration, approach, stent length, treated vessels and complications, are entered in web-based case record forms by the interventionalist. The antiplatelet regimen in the CoBaGI trial consists of aspirin and clopidogrel combined for 12 months followed by aspirin lifelong and applies for both treatment arms. Table 1 presents the schedule of enrollment, interventions and assessments for the CoBaGI trial and Fig. 1 presents the Consolidated Standards of Reporting Trials (CONSORT) study flowchart [25].

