### Outcome

The primary endpoint is the primary patency rate 24 months after stent placement based on intention-to-treat analyses.

The secondary endpoints are (definitions are shown in Table 2):
Primary patency rates at 6 and 12 monthsSecondary patency rates at 6, 12 and 24 monthsFreedom from restenosis at 6, 12 and 24 monthsFreedom from symptom recurrence at 6, 12 and 24 monthsFreedom from re-intervention at 6, 12 and 24 monthsQuality of life at 6, 12 and 24 monthsCost-effectiveness at 6, 12 and 24 months

**Table 2 Tab2:** Definitions

	Definition
Restenosis	> 50% intra-stent stenosis regardless whether the patient had clinical symptoms
Symptom recurrence	Occurrence of presenting symptoms regardless of stent patency
Re-intervention	Intervention due to symptom occurrence in the presence of > 50% intra-stent stenosis, either a reimplantation of stent, or a surgical procedure

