### Blinding

The patient, investigator and the treating physician at the outpatient clinic are blinded for the treatment allocation (BMS or CS). For the duration of the trial the allocated stent will not be disclosed unless there is a medical need (i.e., restenosis, stent fracture).

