### Statistical methods

Descriptive analyses will be provided regarding patient characteristics before randomization. Because this is a randomized controlled trial, statistical tests to detect differences in these baseline characteristics between both intervention arms will not be performed. The following patient characteristics before randomization will be provided: age, gender, Body Mass Index (BMI), smoking status, comorbidity with hypertension, dyslipidemia, diabetes and cardiovascular disease. Furthermore presenting symptoms will be described as abdominal pain, postprandial pain, exercise-related pain, nausea, diarrhea, weight loss and symptom duration. Patient characteristics will be described as numbers and percentages for dichotomous variables, or as means and standard deviations for continuous variables with normal distribution or medians and interquartile ranges (IQRs) for continuous variables if not normally distributed.

The primary analysis will be performed according the intention-to-treat principle. A per-protocol analysis will also be performed for the primary outcome of stent patency for those patients who were treated according to the treatment protocol.

The primary endpoint of stent patency will be analyzed with a “two-sample z-test” for comparison of two proportions. Furthermore, a predictive model for time-to-event will be obtained by proportional hazards regression and Kaplan-Meier analysis to compare patency rates of CS versus BMS. All other continuous outcome measures will be reported as difference in mean improvement between the CS versus the BMS group. Change in quality of life assessed by the validated questionnaires EQ-5D-5 L [26, 27] and SF-36 [28, 29] will be compared between the CS and BMS groups. Furthermore, the costs of both groups will be compared. All costs will be estimated based on actual input in terms of resource use, personnel and indirect costs from loss of productivity assessed by the cost-effectiveness questionnaire.

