## Discussion

The CoBaGI trial is designed to compare the patency rate of BMS (standard care) with CS in patients with CMI based on atherosclerotic mesenteric stenosis. Besides, the study should provide insights into the change in quality of life of patients induced by both stents and their cost-effectiveness. The CoBaGI trial is the first randomized controlled trial to compare BMS with CS in patients with CMI based on an atherosclerotic mesenteric stenosis.

The recently published clinical practice guidelines of the European Society of Vascular Surgery (ESVS) recommend with a low level of evidence (C: expert opinion and/or small studies, retrospective studies) to consider CS over BMS for patients requiring mesenteric artery stenting based a single retrospective study by Oderich et al. [21]. A stronger, level-A recommendation can only be issued based on the results of randomized controlled trials. The optimal design would be a double-blinded controlled trial. Since the physician who performs the endovascular procedure cannot be blinded, the CoBaGI trial is designed as a patient- and investigator-blinded, randomized controlled trial.

The primary endpoint of the CoBaGI trial is primary stent patency assessed with CTA. The primary endpoint is a hard endpoint which can be assessed objectively. The secondary endpoint of symptom recurrence is dependent on reports of patient and investigator. In order to ensure unbiased collection and an objective assessment of the endpoints, blinding of the patient and investigator is important.

To perform a fair comparison between the two stent designs all participating centers will use the same brand/type of BMS as standard of care in the CoBaGI trial. The initiating center, Erasmus MC University Medical Center, had already ample experience with the BMS Palmaz Blue from Cordis for mesenteric stenting and, therefore, this stent was chosen to be used in all participating centers. BMS from different manufacturers are considered comparable in use and outcome although studies comparing BMS from different manufacturers are lacking.

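### Randomisation precedes the angiogram that settles eligibility and treatment, so an operator who may know the arm can decide who is left unstented

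*Protocol article*

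**What the plan says.** The Interventions section of the protocol article gives the order of events. First: "At the start of the endovascular procedure patients are randomized for either a BMS or CS". Then: "During the angiography the stenoses are assessed and if a suspected stenosis is not significant, this vessel will not be treated". Use of the assigned device is tied to two findings on that angiogram, in a sentence that ends by naming that device: "If the stenosis is detected to be significant during angiography and the stenosis length is < 25 mm the stenosis will be treated with the".

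Under Eligibility criteria, finding no stenosis at angiography is an exclusion criterion. The same section requires, before this stage, a consensus diagnosis, a stenosis above 50% on CT angiography and a total stenosis length under 25 mm. The CT may date from up to a year before the consensus diagnosis.

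On blinding, the Blinding section says: "The patient, investigator and the treating physician at the outpatient clinic are blinded for the treatment allocation (BMS or CS"). The interventionalist is not on that list, and the Discussion gives the reason: "Since the physician who performs the endovascular procedure cannot be blinded".

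On analysis, the Outcome section says: "The primary endpoint is the primary patency rate 24 months after stent placement based on intention-to-treat analyses". Statistical methods repeats it: "The primary analysis will be performed according the intention-to-treat principle", with a per-protocol analysis alongside.

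**The concern.** Randomisation protects a comparison only if nothing after it can sort patients by arm. Here one eligibility criterion and the decision to stent both come after allocation. They rest with the one person in the trial who cannot be blinded. Calls on borderline significance or on a length close to 25 mm are matters of judgement, and they could differ between arms if the allocation is known.

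The Discussion gives a reason why the arms might pull differently on length. The longest bare-metal stent available was 24 mm and the longest covered stent 59 mm, and a covered stent blocks a side branch that it crosses while a bare-metal stent does not.

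There is a second consequence. The endpoint is counted from stent placement, so a randomised patient who turns out to have no treatable vessel has no patency value. Applying the exclusion criterion removes that patient after randomisation. Keeping the patient leaves no stent to assess. At stake is whether the primary comparison is the randomised one.

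**Working it through.** **Order of events.** Three statements have to hold together for the concern to stand.

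| Step | What the article says | Section |
|---|---|---|
| 1 | Allocation at the start of the procedure | Interventions |
| 2 | Angiogram then settles significance and length; no stenosis is an exclusion | Interventions; Eligibility criteria |
| 3 | Operator not blinded | Discussion; Blinding |

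All three are in the text. The exact moment at which the operator learns the arm is not stated. The order permits it before the angiogram is read, but does not prove it.

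**Is the problem loss of numbers?** Inputs from Sample size: 63% versus 95%, two-sided alpha 0.05, 80% power, 20% dropout, 42 per arm. For the pooled z-test:

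n = [1.96·√(2·0.79·0.21) + 0.8416·√(0.63·0.37 + 0.95·0.05)]² / 0.32² = (1.129 + 0.446)² / 0.1024 ≈ 24.2, so 25 per arm; 25/0.80 = 31.25, so 32 with dropout.

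This does not reproduce 42, which is larger than needed. The present point does not depend on that. With 42 × 0.80 = 33.6 evaluable per arm (33 rounded down), power is 91.0%. If a further 5% to 20% (assumed) were lost without regard to arm, 31 to 26 per arm would remain and power would be 89.1% to 82.9%. So the issue is bias, not power.

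**Does one patient decide the result?** Pooled z-test, 34 per arm (33.6 rounded up). Expected failures at the planned rates: bare-metal 0.37 × 34 = 12.6, covered 0.05 × 34 = 1.7.

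| Bare-metal failures | Covered failures | p |
|---|---|---|
| 13 | 2 | 0.0013 |
| 13 | 3 | 0.004 |
| 13 | 5 | 0.028 |
| 13 | 6 | 0.059 |
| 12 | 2 | 0.0027 |
| 12 | 5 | 0.0499 |
| 8 | 2 | 0.040 |
| 8 | 3 | 0.0996 |

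At the planned rates, one extra covered-stent failure changes nothing. With 13 bare-metal failures it takes four more to lose significance. A single patient decides only if bare-metal patency is well above plan (8/34 failures is 76% patency).

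**What could selective exclusion do?** Suppose true patency p is equal in both arms, and k of 42 covered-stent patients who would have failed are removed after randomisation. Apparent covered-stent patency becomes 42p/(42 − k). The rejection rate of the two-sided pooled z-test, by exact enumeration with 42 and 42 − k patients, is:

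| p | k | Apparent patency | Shift (points) | Rejection rate |
|---|---|---|---|---|
| 63% | 0 | 63.0% | 0 | 5.5% |
| 63% | 2 | 66.15% | 3.15 | 6.4% |
| 63% | 4 | 69.6% | 6.6 | 9.9% |
| 63% | 6 | 73.5% | 10.5 | 16.7% |
| 80% | 0 | 80.0% | 0 | 5.2% |
| 80% | 2 | 84.0% | 4.0 | 7.4% |
| 80% | 4 | 88.4% | 8.4 | 16.6% |
| 80% | 6 | 93.3% | 13.3 | 42.2% |

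Removing k realised failures instead, as a variant of the model, gives 11.5% (p = 63%) and 21.7% (p = 80%) at k = 4. Both k and the 80% are assumptions. This is the worst case, because every removed patient is taken to be a future failure in one arm.

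**The case against.** The other side has a good case, and most of it stands.

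- **Screening comes first.** Significance on CT, stenosis length and the consensus diagnosis are all assessed before allocation, and every patient is discussed at one of two specialised centres. The angiogram mostly confirms. The number affected is probably small. Against that, the CT may be old by the time of the procedure, and the Interventions section itself provides for disagreement.
- **The significance rule is per vessel:** "if a suspected stenosis is not significant, this vessel will not be treated". A reader might infer that anyone failing a check goes without a stent. The text does not say that. A patient with disease in both arteries may have one left alone and still receive the allocated stent, and nothing says that a longer stenosis goes unstented. Only a patient with no treatable vessel clearly has no stent.
- **Intention-to-treat is declared.** A reader might infer that unstented patients are dropped, or that the analysis cannot be done. Neither is stated. A rule for scoring such patients is normal content for an analysis plan, which is not shown, so its absence is no fault here.
- **Foresight is limited.** An operator cannot tell which patients will fail at 24 months, so the worst-case figures above are an upper illustration.
- **A reader might infer that the result hangs on a single patient.** At the planned rates it does not.
- **It is late.** With 71 of 84 enrolled by September 2018, a change of timing reaches at most 84 − 71 = 13 patients.

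What survives is the order itself. An exclusion criterion and the treatment decision sit after allocation, with an unblinded operator, when they could sit before it.

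**Conclusion.** The concern holds as a design weakness that permits bias. It does not show that bias occurred. The article fixes the sequence in its own words, so this is not a detail left to a fuller document.

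The size is unknown, because no count of randomised-but-not-stented patients is given. At the planned effect a few such patients would not overturn the result. If the true effect is smaller, a few selective exclusions could matter: four of 42 in one arm would take the false-positive rate to about 10% (63% true patency) or 17% (80%). That rests on equal true patency, one-sided removal, and every removed patient being a would-be failure. It also assumes that the operator knows the arm before reading the angiogram, which the text allows but does not state.

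Severity: should be fixed.

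**What to change.** **Patients still to be enrolled** (at most 13 at September 2018): release the web allocation only once the diagnostic angiogram has documented at least one stenosis meeting the protocol's own criteria. Sample size, allocation ratio and stratification stay as they are.

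**Patients already randomised:** state that all of them stay in the primary intention-to-treat set whatever the angiogram showed. Confine any angiographic exclusion to a secondary analysis. Report by arm how many were randomised but not stented. If the angiograms of those patients can be re-read by someone blind to the arm, that would strengthen the secondary analysis, but it may need an extra reader and is optional.

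**Cost:** a short amendment, and a web call made some minutes later during the procedure. The reporting by arm should need little beyond the procedural details already entered in the case record forms.
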